### Concomitant and forbidden drugs

Drugs recommended in the 2014 Chinese guidelines [10] for the diagnosis and treatment of heart failure are permitted. They include angiotensin-converting enzyme inhibitors (ACEIs) or angiotensin-receptor blockers (ARBs), β-blockers, diuretics, aldosterone-receptor antagonists (AAs), digoxin, and ivabradine. However, in the course of the study, the patient’s treatment is required to remain stable as far as possible. If the patient is in a serious condition and the treatment plan has to be adjusted, the clinician should operate according to the guidelines and inform the researcher of relevant information in an accurate and detailed manner. Other traditional Chinese medicines that may alleviate CHF—whether it is a decoction or a Chinese patent medicine—are prohibited. Drugs that are not related to CHF symptoms are permitted. The name, duration, and dosage of any other drugs taken will be recorded in the CRF.

## Outcome measures

### Laboratory tests

Routine laboratory tests (complete blood count, routine urinalysis, and serum chemistry profile) will be performed in the local laboratories of the participating institutions. Serum NT-proBNP levels will be measured by using an NT-proBNP (human) ELISA kit in the Research Center, Beijing University of Chinese Medicine, Beijing, China.

### Primary outcome

The primary outcome is the proportion of patients in the QSG group, compared with the placebo group, demonstrating a more than 30% decrease in NT-proBNP level during 12 weeks of treatment.

On the day of inclusion, serum NT-proBNP will be taken as the baseline level of participants who will be enrolled and randomized for this trial before taking the QSG or placebo.

### Secondary outcomes

The secondary outcomes of this study are as follows:Composite cardiac events (CCEs): CCEs are defined as death, readmission for heart failure and other cardiovascular events such as acute coronary syndrome, serious cardiac arrhythmias, cardiac shock, etc. We will carry out continuous monitoring of CCEs and evaluate the links between CCEs and test drugs. The assessments of safety and tolerability will be based on spontaneous reports of adverse events, vital signs and laboratory testsNYHA functional classification: based on the NYHA functional classification, the investigators will grade the severity of functional limitation and patient estimates of how far they are able to walk before they become breathless6-minute walking distance (6MWD): participants will be instructed to walk as far as possible over a period of 6 min. This test is scored in rounded meters walked in 6 minLVEF: left ventricular ejection will be obtained from all participants by an experienced echocardiographic technician in each local participating center, who is blind to the allocation of the patientsPatient quality of life: The Chronic Heart Failure Quality of Life Scale of Integrated Chinese and Western Medicine [13] will be used to evaluate all patients. An additional file shows this in more detail (see Additional file 2)TCM syndrome integral scale: TCM symptoms of all patients will be assessed through TCM syndrome integral scale

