## Methods/design

### Objective

The objective of this study is to evaluate the safety and efficacy of QSG in a large and varied CHF population.

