## Randomization

An independent statistician who is unaware of the design and purpose of the study will generate a randomization table by using Statistical Analysis System (SAS, version 9.4). The 200 patients will be randomly allocated in a 1:1 ratio to either the QSG treatment group or the placebo group. The randomization will be stratified by study site. According to the design of the random program, the researcher will open one random envelope and obtain a randomization number for a patient on the day of inclusion. Both investigators and participants will be blind to the allocations.

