## Data collection and management

A CRF will be used for each participant to collect relevant data. The participants will be evaluated every 4 weeks during the study. Data on CCEs, NYHA functional classification, 6MWD, patient quality of life and the TCM syndrome integral scale will be collected at each visit (week 0 ± 3 days, week 4 ± 3 days, week 8 ± 3 days, and week 12 ± 3 days). The NT-proBNP and LVEF will be measured only at the first and the last visit (week 0 ± 3 days and week 12 ± 3 days). The Standard Protocol Items: Recommendations for Interventional Trials (SPIRIT) flowchart of the trial can be found in Fig. 2.

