## Adverse events (AEs)

An undesirable, unexpected sign, symptom, or disease that occurs during clinical observation will be identified as an adverse event, whether or not it has a causal relationship with the test drug. We will carry out continuous monitoring of AEs and evaluate the links between AEs and test drugs. The chief investigator will be informed of any serious AEs immediately and will cooperate with clinicians in dealing with AEs in a timely manner to protect the subjects as much as possible.

All treatment-related serious adverse events will be recorded and reported to the Research Ethics Committee in good time. The chief investigator will be responsible for all AE reporting. Prior to study initiation, all investigators involved in the study will be trained in the procedures to be followed and in the forms to be used during the study.

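### Symptomatic adverse events are to come from spontaneous reports although every patient is seen every 4 weeks, so that part of the safety comparison is likely to be under-counted and imprecise

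*Protocol article*

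**What the plan says.** The Objective section makes safety a joint aim: "The objective of this study is to evaluate the safety and efficacy of QSG in a large and varied CHF population".

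The source of safety data is named in the composite cardiac events (CCE) item of Secondary outcomes: "The assessments of safety and tolerability will be based on spontaneous reports of adverse events, vital signs". The sentence ends by adding laboratory tests, which the Laboratory tests section specifies: "Routine laboratory tests (complete blood count, routine urinalysis, and serum chemistry profile) will be performed in the local laboratories".

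The Adverse events section defines an event broadly: "An undesirable, unexpected sign, symptom, or disease that occurs during clinical observation will be identified as an adverse event", whatever its cause. It then states: "We will carry out continuous monitoring of AEs and evaluate the links between AEs and test drugs". It gives no method for eliciting symptoms.

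Data collection and management sets the visits ("The participants will be evaluated every 4 weeks during the study", that is weeks 0, 4, 8 and 12) and lists visit data: "Data on CCEs, NYHA functional classification, 6MWD, patient quality of life and the TCM syndrome integral scale will be collected at each visit". Adverse events are not in that list.

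**The concern.** How symptoms are ascertained is settled when data are collected, and no later analysis can recover a symptom that was neither asked about nor mentioned. Volunteered reporting tends to miss non-serious complaints, and how much it misses can differ between patients and between the three centres. The absolute difference between arms shrinks with the counts. At stake is the reading of a quiet safety table: few symptomatic events could mean that the granules are well tolerated, or only that patients did not bring symptoms up. The article promises high-quality evidence on safety, and this part of the evidence would not separate the two explanations.

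**Working it through.** **1. Which harms depend on volunteering?**

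| Type of harm | Source named in the article | Depends on the patient volunteering it? |
|---|---|---|
| Laboratory abnormality | Blood count, urinalysis, serum chemistry | No |
| Vital-sign change | Vital signs | No |
| Death, heart failure readmission, acute coronary syndrome, arrhythmia, shock | CCEs, collected at each visit | No |
| Non-cardiac symptoms | Spontaneous reports | Yes, as written |

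The point is confined to the last row. There, spontaneous reporting and continuous monitoring are in tension: the second suggests active follow-up, and the first is the only method named for symptoms.

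**2. Is there a figure in the plan to check?** Only the sample size for NT-proBNP. n = (1.960 + 0.842)² × [0.3198 × 0.6802 + 0.53 × 0.47] / 0.2102² = 82.9, so 83 per arm, and N = 2 × 83 × 1.2 = 199.2, about 200. It reproduces but says nothing about adverse events. The article gives no adverse event rate and no capture fraction.

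**3. Illustration of direction.** From the article: "The 200 patients will be randomly allocated in a 1:1 ratio to either the QSG treatment group or the placebo group", so 100 per arm, with two-sided α = 0.05. Assumed: true rates p₀ (placebo) and p₁ = 2p₀ (QSG), and the same capture fraction c in both arms, so the observed rates are c·p₀ and c·p₁. Power is the exact sum over x, y = 0…100 of Bin(x; 100, c·p₀) × Bin(y; 100, c·p₁) for the pairs with |z| > 1.96, where z = [(y − x)/100] / √[2p̄(1 − p̄)/100] and p̄ = (x + y)/200. This is the uncorrected χ² test.

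| Capture c | True rates 10% vs 20% | True rates 15% vs 30% |
|---|---|---|
| 100% | 0.518 | 0.729 |
| 70% | 0.373 | 0.542 |
| 50% | 0.270 | 0.397 |
| 30% | 0.154 | 0.241 |

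If only 80 per arm contribute (100 less the planned 20% dropout), 15% vs 30% gives 0.635 at full capture and 0.322 at 50%.

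**4. Bias or precision?** With equal capture the ratio c·p₁ / c·p₀ = p₁/p₀ is unchanged, while the absolute difference c(p₁ − p₀) shrinks in proportion to c. For 10% vs 20%, the standard error of the log risk ratio is √[(1 − 0.10)/10 + (1 − 0.20)/20] = √0.13 = 0.36 at full capture. At 50% capture it is √[(1 − 0.05)/5 + (1 − 0.10)/10] = √0.28 = 0.53. The loss is in counts and precision.

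**5. What asking adds.** A prompt also brings out unrelated complaints. If it added 10 percentage points to both arms (assumed), 10% vs 20% would become 20% vs 30%, and the same calculation gives power 0.371, practically the 70%-capture figure of 0.373. The full gap between the 100% row and the lower rows therefore overstates what the change would recover.

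**The case against.** The strongest reply is that one clause in the CCE item should not outweigh the dedicated adverse events section. That section covers signs and diseases as well as complaints, promises continuous monitoring, and says that investigators will be trained in procedures and forms not reproduced in the article. The article condenses a fuller protocol, and the SPIRIT schedule (Fig. 2), which is not shown, may list adverse event assessment by visit. The visit list also leaves out vital signs and laboratory tests, so the absence of adverse events from it proves little. Spontaneous reporting alongside such measurements is a recognised method, and no test of adverse events is powered here.

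Much of this stands. The visit list is weak evidence, and it cannot be said that nobody will ask. It does not remove the point, because the article does not merely omit the method: it names one, and neither the training sentence nor a visit schedule would change that wording.

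A reader might infer that the whole harm comparison rests on what patients volunteer. The documents do not support this, since laboratory tests, vital signs and CCEs are collected independently. A reader might also infer a bias between arms. That is not supported either: the trial is double-blind and randomization is stratified by site, which favours similar capture in both arms.

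**Conclusion.** The point holds for symptomatic, non-cardiac adverse events. If the stated method is followed, these are likely to be under-counted and unevenly captured across patients and sites. The comparison between arms would be less precise, and a low count would say little in favour of safety. The primary outcome is untouched.

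The size of the loss cannot be derived from the documents. The power figures depend on assumed event rates, an assumed doubling and assumed equal capture fractions, and the main table leaves out the background complaints that asking would add. They show direction only. It is a cheap improvement to make, and the sections on safety data need to agree with one another in any case.

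**What to change.** Reword the safety sentence under Secondary outcomes along these lines: *At weeks 4, 8 and 12 every patient in both arms is asked the same open, non-leading question about any new or worsened symptom since the last visit. Answers are recorded on the CRF, in addition to events reported spontaneously between visits, vital signs and laboratory tests.*

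Add adverse events to the visit data in Data collection and management, and state in the Adverse events section that this enquiry is part of continuous monitoring. Report elicited and volunteered events by arm, both combined and separately.

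The cost is one scripted question and one CRF line at three existing visits, plus the protocol wording. No extra visit, sample or patient is needed. The drawback is more minor events to record and higher background rates in both arms, which offsets part of the gain in power. The Trial status section reports that recruitment had not begun, so at that stage the change could cover every patient.

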## Data collection and management

A CRF will be used for each participant to collect relevant data. The participants will be evaluated every 4 weeks during the study. Data on CCEs, NYHA functional classification, 6MWD, patient quality of life and the TCM syndrome integral scale will be collected at each visit (week 0 ± 3 days, week 4 ± 3 days, week 8 ± 3 days, and week 12 ± 3 days). The NT-proBNP and LVEF will be measured only at the first and the last visit (week 0 ± 3 days and week 12 ± 3 days). The Standard Protocol Items: Recommendations for Interventional Trials (SPIRIT) flowchart of the trial can be found in Fig. 2.

**Fig. 2 Fig2:**
[figure not shown]
Standard Protocol Items: Recommendations for Interventional Trials (SPIRIT) flowchart

All documents collected in this study will be stored safely. Apart from the informed consent, in all other documents in this study, participants will be referred to by a specific randomization number rather than by their names. The study documentation will be archived for at least 5 years after the study.

## Adverse events (AEs)

An undesirable, unexpected sign, symptom, or disease that occurs during clinical observation will be identified as an adverse event, whether or not it has a causal relationship with the test drug. We will carry out continuous monitoring of AEs and evaluate the links between AEs and test drugs. The chief investigator will be informed of any serious AEs immediately and will cooperate with clinicians in dealing with AEs in a timely manner to protect the subjects as much as possible.

All treatment-related serious adverse events will be recorded and reported to the Research Ethics Committee in good time. The chief investigator will be responsible for all AE reporting. Prior to study initiation, all investigators involved in the study will be trained in the procedures to be followed and in the forms to be used during the study.

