### Data analysis

Data entry and management will be completed by an independent data administrator to ensure data accuracy. A professional statistician will perform the data analysis for the results. We will use the intent-to-treat principle to analyze the efficacy and safety of QSG. For continuous variables, the independent two-sample Student’s *t* test will be used for comparisons between the two study groups, and the paired test will be used for intra-group comparisons. The *χ*2 test will be used for categorical variables. When continuous data distribution is not normal, the Wilcoxon test will be used. *P* < 0.05 is considered to be statistically significant, and all tests are two-tailed.

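### The adverse event section contradicts itself on which harms are recorded, leaving serious non-cardiovascular events and anticipated non-serious events to individual judgement

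*Protocol article*

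**What the plan says.** All of the following is in the protocol article.

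- **Adverse events (AEs), definition.** "An undesirable, unexpected sign, symptom, or disease that occurs during clinical observation will be identified as an adverse event", and this applies "whether or not it has a causal relationship with the test drug".
- **Same section, monitoring.** "We will carry out continuous monitoring of AEs and evaluate the links between AEs and test drugs".
- **Same section, notification and responsibility.** "The chief investigator will be informed of any serious AEs immediately", and "The chief investigator will be responsible for all AE reporting".
- **Same section, recording and ethics reporting.** "All treatment-related serious adverse events will be recorded and reported to the Research Ethics Committee in good time".
- **Blinding.** Serious adverse events are listed by outcome (death, threat to life, hospital admission or its prolongation, permanent disability, cancer, birth defect, overdose). Relatedness is not a condition.
- **Secondary outcomes.** "CCEs are defined as death, readmission for heart failure and other cardiovascular events", with acute coronary syndrome, serious arrhythmia and cardiac shock as examples. Under Data collection and management these composite cardiac events (CCEs) are collected at weeks 0, 4, 8 and 12. Safety also draws on spontaneous reports, vital signs and laboratory tests.

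**The concern.** Two qualifiers narrow what is captured. The word *unexpected* in the definition, read literally, excludes an event that an investigator anticipates in a patient with heart failure. Expectedness is a property that an adverse event may or may not have. It is not what makes something an adverse event. The words *treatment-related* in the serious event sentence govern the verb *recorded* as well as *reported*, and no other sentence says which serious events are recorded.

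Safety is half of the stated objective. In a placebo-controlled trial, the evidence on whether a drug causes an event comes from comparing its frequency between the arms. If each event must first be judged related before it is written down, that comparison is made on a filtered set. A harm that nobody suspects of being due to the drug is the one most likely to be filtered out. With three centres, the two qualifiers may also be applied differently from site to site.

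**Working it through.** The point is textual, and no design figure in the article bears on it. The check is to follow each class of event through the rules as written.

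| Event | Definition: any cause, but unexpected | Chief investigator told | Recording sentence: related only | Collected as CCE |
|---|---|---|---|---|
| Death | depends on expectedness | yes | only if judged related | yes |
| Heart failure readmission, acute coronary syndrome, serious arrhythmia, shock | depends on expectedness | yes, if serious | only if judged related | yes |
| Serious non-cardiovascular event (e.g. hepatic, renal, electrolyte or infectious admission) | depends on expectedness | yes | only if judged related | no |
| Non-serious event, anticipated | excluded if read literally | not required | not covered | no, unless it meets the CCE definition |
| Non-serious event, not anticipated | included | not required | not covered | no, unless it meets the CCE definition |

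Three things follow.

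1. **The section conflicts with itself.** The definition sets causality aside, the notification rule covers every serious event, and the recording rule brings causality back. Taken literally, an unexpected minor event unrelated to the drug counts as an adverse event, while no sentence promises to record a serious unrelated one. The Blinding list, which turns on outcome alone, sides with the broader reading.

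2. **Fatal and cardiovascular events are not lost.** The Background cites 16.5% mortality within one year in an international cohort. At a constant hazard over 12 weeks this gives 1 − (1 − 0.165)^(12/52) ≈ 0.041, and 0.041 × 200 ≈ 8 deaths. That is a rough upper guide, because the trial enrols clinically stable NYHA class II–III patients aged 18 to 75. Every such death is a CCE, collected by arm whatever cause is assigned. The same holds for heart failure readmissions.

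3. **The third and fourth rows are exposed.** Let p_Q and p_P be the true risks of a serious non-cardiovascular event in the two arms, and f the fraction judged related. If recording follows the sentence as written, the recorded risks are f·p_Q and f·p_P, and the recorded difference is f·(p_Q − p_P). If blinding keeps f equal in the two arms, the ratio is preserved, but only a fraction f of the events is available to estimate it. For a type of event that nobody attributes to the drug, f is near zero and there is nothing left to compare. The documents give no value for p_Q, p_P or f, so the loss cannot be put as a number.

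**The case against.** The strongest reply is that the recording sentence is really about what goes to the ethics committee and does not define the safety dataset. The same section promises continuous monitoring of adverse events, immediate notification of any serious one, and a single role answerable for all reporting. *Unexpected* may be a loose rendering of untoward. Vital signs, blood count, urinalysis and serum chemistry would pick up many hepatic, renal or electrolyte disturbances in any case.

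Much of this stands, and it keeps the point moderate. It does not remove it. The sentence says recorded before it says reported. Notification is not a rule for data capture, and naming who is responsible does not fix the scope. A laboratory value shows an abnormality but does not by itself register an admission as a serious event.

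Three stronger readings are tempting, and the documents do not support them.

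- *That safety capture is confined to unexpected and treatment-related events, so that most harm data would be missed.* The CCE outcome, the causality-neutral definition and the laboratory and vital-sign data all contradict this. Nor does anything in the article show that blinded investigators would call most serious events unrelated.
- *That analysing safety by intention to treat dilutes event rates by a fifth.* The plan does say "We will use the intent-to-treat principle to analyze the efficacy and safety of QSG", and it keeps patients without follow-up in that population. But the 20% is a dropout allowance in the sample size. Rates would fall to 0.8 of their true value only if every dropout left with no follow-up at all. Patients who leave after week 4 or week 8 have already contributed data. Equal dropout in the two arms would leave the risk ratio unchanged.
- *That the lack of a scripted adverse event question at each visit, or of a separate treated-patient safety set with exposure time, is a defect.* These are details of the CRF or the analysis plan, which an article commonly leaves out.

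**Conclusion.** The point holds as an internal contradiction with a limited consequence. The section gives incompatible rules on which harms count and which serious events are recorded, and it does so by express wording, not by omission. Followed literally, a serious non-cardiovascular event judged unrelated need not be recorded, and an anticipated non-serious event need not count as an adverse event. For those two classes the randomised comparison is weakened by an amount that the documents do not allow one to calculate. Deaths, heart failure readmissions and other cardiovascular events remain fully comparable between the arms.

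Severity is moderate. This rests on two assumptions: that sites would apply the section as written, and that the full protocol or the CRF, neither of which is shown, does not already override it with a broader rule.

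**What to change.** In the section Adverse events (AEs):

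- Delete *unexpected* from the definition. If expectedness is needed for regulatory purposes, record it as a separate attribute.
- Reword the recording sentence so that all serious adverse events, as listed under Blinding, are recorded whatever their judged relationship to treatment and tabulated by arm. Keep relatedness as a recorded attribute, not as a condition for entry.
- State separately which serious events go to the ethics committee, and reconcile that with the rule that the chief investigator is told of any serious event.

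The cost is a short change of wording, a few more CRF entries and possibly a few more reports. Sample size, visits and the analysis of the primary outcome are unaffected. The article says that no patient had yet been recruited, so the change could be made before enrolment and would apply to every participant.
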